# Single Incision non-thoracoscopic Nuss procedure for children with pectus excavatum: protocol for a multicenter, non-masked, randomized controlled trial

**DOI:** 10.3389/fsurg.2023.1210452

**Published:** 2023-07-19

**Keywords:** pectus excavatum, single incision, Nuss procedure, multicenter, randomized controlled trial

## Abstract

**Background:**

Nuss procedure is the most common method of surgical treatment to pectus excavatum (PE). A significant percentage of surgeons choose to use thoracoscopic assistance during the Nuss procedure (TNP) to avoid cardiac injury. However, our previous findings confirm the safety of single incision Non-thoracoscopic Nuss Procedure (SINTNP). Hence, Further studies, particularly prospective randomized controlled trials, are necessary to assess the value of SINTNP for PE.

**Methods:**

This study is a prospective, superiority, multicenter, non-masked, randomized controlled trial that investigates the outcome and hospitalization medical expense of SINTNP compared to TNP for PE. A total of 320 eligible patients according to sample size calculation by retrospective data will be randomly assigned to the SINTNP group or the TNP group at a 1:1 ratio using stratified blocked randomization and the zone length was set as four. Patients aged between 3 and 18 years old for the first surgery and without combination of complex anomalies such as Marfan syndrome and congenital heart disease will be considered for the study. The co-primary endpoint is thoracic related complications and medical expense during hospitalization. Thoracic related complications were defined as pneumothorax, pleural effusion, pneumonia and incision infection. The secondary endpoints include surgery duration and length of hospital stay.

The registration number for this study protocol is ChiCTR230073081 (Chinese Clinical Trial Registry, A Primary Registry of International Clinical Trial Registry Platform, World Health Organization).

## Background

1.

Pectus excavatum is the most common anterior chest wall deformity in children (1). The Nuss procedure is the appropriate method for treating pectus excavatum in the majority of patients (2). Nuss initially reported a minimally invasive technique using bilateral incisions without the assistance of thoracoscopy (3). Subsequently, in a survey of members of the American Association of Pediatric Surgeons, 61% of members used thoracoscopic assistance during Nuss surgery to reduce the risk of cardiac or pulmonary injury (4). [name] himself also emphasized that thoracoscopic assistance has been highly recommended since 1998 (5). Hence, the majority of surgeons tend to use thoracoscopic assistance in Nuss surgery (6), especially in adults (7).

However, the situation in the field of children may be different. Trained surgeons can safely pass bar through the space behind the sternum without relying on thoracoscopy in children because children's sternum is softer and more malleable. Only 49% of members of the Chinese Association of Thoracic Surgeons consider thoracoscopy to be a necessary method to avoid heart injury during the Nuss procedure (8). Additionally, if unilateral fixation can ensure the stability of the steel plate, then bilateral incisions are not necessary. Our center has been attempting modified single incision non-thoracoscopic Nuss procedure (SINTNP) since 2017 and has completed over 400 such surgeries to date, without any cardiac injury. The specific method of surgery can be found in our previous report (9, 10).

We speculate that modified single incision non-thoracoscopic Nuss procedure can reduce hospitalization costs, the proportion of thoracic-related complications, and the length of hospital stay in patients. Therefore, we conducted this multicenter randomized controlled trial to confirm the clinical value of SINTNP for pediatric patients compared with the thoracoscopic Nuss procedure (TNP) with bilateral incision.

## Methods/design

2.

This study aims to explore whether SINTNP can bring clinical benefits to patients with PE. All the design and analysis procedures will be carried out as shown in Figure 1, reported according to the Standard Protocol Items: Recommendations for Interventional Trials (SPIRIT) checklist (11) (Supplementary Table S1).

**Figure 1 F1:**
[figure not shown]
Flow chart of the study. SINTNP,single incision non thoracoscopic assisted Nuss surgery; TNP, thoracoscopic Nuss procedure.

### Objectives

2.1.

#### Primary objectives

2.1.1.

The coprimary objectives of the study are to assess differences in thoracic-related complications and medical expenses during hospitalization of PE patients undergoing SINTNP or TNP.

#### Secondary objectives

2.1.2.

Secondary objectives were surgery duration and length of hospital stay.

### Trial design and study setting

2.2.

The study is a multicenter, non-masked, randomized controlled trial including patients with PE aged between 3 and 18 years old for the first surgery and without a combination of complex anomalies.

The participants will be randomly assigned to the SINTNP or TNP group with a balance of 1:1. Participants will be allocated as evenly as possible to four hospitals in western China. The sponsor institution was Children's Hospital of Chongqing Medical University. This multicenter study will also be conducted in Chengdu Women and Children's Central Hospital, Chongqing Three Gorges Central Hospital and Qujing Maternal and Child Health Hospital.

Due to objective conditions, the participants in the four centers cannot be completely balanced, but the participants in any center will not exceed 50% of the total number or be less than 15% of the total number. Independent statisticians will perform noninferiority tests for comparisons of SINTNP to TNP.

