### Sample size and recruitment

2.6.

Medical expense during hospitalization is the primary outcome indicator of this study because it can objectively evaluate the financial burden of the patient's family. Based on our retrospective research data on surgeries over the past three years, the average cost of the TNP group was 30,250 RMB, while the average cost of the SINTNP group was 28,157 RMB. The standard deviation will be set as 2,000, and the superiority margin will be set as 1,500. The sample size will be calculated to require at least 141 children in each group.

The proportion of thoracic-related complications was approximately 9.6% in SINTNP and 13.6% in nonthoracoscopic-assisted Nuss surgery with double incision. The sample size calculation requires over 3,000 people per group according to the proportion of thoracic-related complications, and currently, we are unable to recruit so many patients. We will truthfully describe this recruitment-related limitation in the officially published article. Considering a 10% to 15% withdrawal and dropout rate, each group will ultimately include 160 children.

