### Statistical methods

2.11.

Continuous data will be presented as the means with standard deviations (SDs) or medians with interquartile ranges (IQRs). The Kolmogorov–Smirnov test will be used to evaluate normality. Continuous data will be compared between the two groups by unpaired t test (normal distribution) or the Mann‒Whitney *U*-test (nonnormal distribution). A chi-square test will be used to compare categorical variables between two groups. Pre-protocol analysis (PP) will be performed with data of participants finishing the whole study and intention to treat analysis (ITT) will be used in full analysis set. Inter group analysis across centers were performed to evaluate the influence of bias and the reliability of the overall study.

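### The trial is labelled superiority and sized for a saving of more than 1,500 RMB, but section 2.2 orders noninferiority tests with no endpoint or margin, and the tests in section 2.11 do not carry the 1,500 RMB margin

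*Protocol article*

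**What the plan says.** All references are to the protocol article.

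- **Abstract, Methods:** "This study is a prospective, superiority, multicenter, non-masked, randomized controlled trial".
- **Section 2.1.1 (Primary objectives):** "The coprimary objectives of the study are to assess differences in thoracic-related complications and medical expenses during hospitalization". It gives no direction and no margin.
- **Section 2.2 (Trial design and study setting):** "Independent statisticians will perform noninferiority tests for comparisons of SINTNP to TNP". It names no endpoint, and no noninferiority margin appears anywhere in the article.
- **Section 2.6 (Sample size and recruitment):** "Medical expense during hospitalization is the primary outcome indicator of this study". The planning values are "the average cost of the TNP group was 30,250 RMB" and "the average cost of the SINTNP group was 28,157 RMB". Then: "The standard deviation will be set as 2,000, and the superiority margin will be set as 1,500". The result is at least 141 children per group, raised to 160 for withdrawal and dropout. The section also says that sizing on complications would need more patients than can be recruited.
- **Section 2.11 (Statistical methods):** "Continuous data will be compared between the two groups by unpaired t test (normal distribution"), with Mann-Whitney as the alternative for nonnormal data and chi-square for categorical data. No null value, margin, sidedness or alpha is given.

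**The concern.** Superiority by a margin, noninferiority and a plain test of difference are three different claims with three different thresholds. The article uses the language of the first in the abstract and section 2.6 and orders the second in section 2.2. In section 2.11 it names tests that, run in their usual form, deliver the third. Nothing in the text says which governs the primary conclusion on expense.

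At stake is whether the same data count as success or failure. An analyst who runs the section 2.11 tests in their default form could report a positive primary result for a saving far below the margin used to size the trial. An analyst who follows section 2.2 would first have to choose a margin and an endpoint, possibly with the data in hand.

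**Working it through.** **Inputs.** From section 2.6: mean cost 30,250 RMB (TNP) and 28,157 RMB (SINTNP), SD 2,000, margin 1,500, n = 141 per group, 160 after allowance for dropout. From section 2.2: 1:1 allocation. Alpha, sidedness and power are not stated, so they are varied below.

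**Step 1: reproduce the 141.**

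Expected saving = 30,250 − 28,157 = 2,093 RMB. Net of the margin = 2,093 − 1,500 = 593 RMB.

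n per group = 2 × SD² × (z_alpha + z_power)² / (net effect)²

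One-sided 0.05, 80% power: 2 × 2,000² × (1.645 + 0.842)² / 593² = 140.7, rounded up to **141**. This matches exactly.

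Other common choices do not match:

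| Alpha | Power | n per group |
|---|---|---|
| one-sided 0.05 | 90% | 195 |
| one-sided 0.025 (two-sided 0.05) | 80% | 179 |
| one-sided 0.025 (two-sided 0.05) | 90% | 240 |

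**Step 2: size under the other hypotheses, at 80% power.** Each range runs over one-sided 0.05 and one-sided 0.025.

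- Superiority against zero, true saving 2,093: 12 to 15 per group.
- Noninferiority, borrowing 1,500 RMB as the margin (an assumption, since none is given): 22 to 28 per group if the true difference is zero, and 4 to 5 if SINTNP is 2,093 RMB cheaper.

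Of these, only the hypothesis of a saving above 1,500 RMB is near 141.

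**Step 3: success thresholds with 141 per group.**

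SE = 2,000 × √(2/141) = 238.2 RMB.

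- Two-sided 5% test against zero: observed saving above 1.96 × 238.2 = about 467 RMB.
- Margin test, one-sided 0.05: above 1,500 + 1.645 × 238.2 = about 1,892 RMB. At one-sided 0.025: about 1,967 RMB.
- Noninferiority with the borrowed 1,500 RMB margin, one-sided 0.05: met unless SINTNP is observed to cost more than 1,500 − 392 = about 1,108 RMB extra.

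An observed saving of 800 RMB would therefore pass the test against zero and this noninferiority test, and fail the test behind the sample size.

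**Step 4: how often the two-sided 5% test against zero is significant, 141 per group.**

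Probability ≈ Φ(true saving / 238.2 − 1.96).

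| True saving (RMB) | Test against zero | Test against 1,500 |
|---|---|---|
| 500 | about 55% | below its alpha |
| 1,000 | about 99% | below its alpha |
| 1,500 | above 99.99% | its alpha: 5% if one-sided 0.05, 2.5% if one-sided 0.025 |

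**Step 5: power of the margin test at the expected saving of 2,093 RMB.**

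- One-sided 0.05: 80.1% with 141 per group, 84.3% with 160.
- One-sided 0.025: 70.2% with 141 per group, 75.6% with 160.

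**The case against.** The strongest reply is that section 2.11 does not fix a null of no difference. It names tests, not null values. An unpaired t test can be run against 1,500 RMB, and its confidence interval can be read against 1,500 RMB. A condensed article may leave that to the analysis plan. This stands: a reader might infer that the article commits to an equality test, or that its tests could never show a saving above 1,500 RMB, and the text supports neither for the t test. What remains is that section 2.11 omits the margin, and that its Mann-Whitney branch, in standard form, cannot test a margin on mean cost.

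Second, a reader might infer that the planned false-positive rate at a 1,500 RMB saving is 5%. The article states no alpha, so 5% is only inferred from the match to 141.

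Third, a reader might infer that error control is lost altogether. It is lost only relative to the 1,500 RMB null. The wording of section 2.1.1, and the hope of lower costs in the Background, also fit a null of zero, under which detecting a 500 RMB saving is a correct result. But a zero null does not explain 141 per group.

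Fourth, the noninferiority sentence may have been meant for complications, where section 2.6 concedes that a powered comparison is out of reach. The text cannot settle this, so it is not safe to conclude that the sentence is simply an error to delete. If that was the intention, the sentence still needs its endpoint and margin.

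None of these replies reconciles a superiority design with an unspecified order for noninferiority tests. An unseen analysis plan would not remove that conflict from the protocol.

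**Conclusion.** The point holds as a contradiction between the abstract and section 2.6 (superiority, with a 1,500 RMB margin) and section 2.2 (noninferiority, with no endpoint or margin). Section 2.11 compounds it by not carrying the margin. The sample-size arithmetic is not at fault: 141 per group follows from the stated means, SD and margin once one-sided 0.05 and 80% power are assumed.

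The consequence is large. The observed saving needed for success is about 467 RMB on one reading and about 1,892 RMB on another. At a true saving of exactly 1,500 RMB, the test against zero is almost always significant, while the margin test rejects at 5% or 2.5%. These figures assume SD 2,000 in both groups, 141 analysed per group and approximately normal means. The direction does not depend on which alpha was intended. Because it decides whether the primary cost claim succeeds, it should be settled before any data are analysed.

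**What to change.** 1. **Expense.** State H0: mean(TNP) minus mean(SINTNP) is at most 1,500 RMB; H1: it exceeds 1,500 RMB. State the alpha, sidedness and power used for sizing. Declare success only if the lower confidence bound of the mean difference, at that alpha, exceeds 1,500 RMB. Use this bound in place of the Mann-Whitney branch, by bootstrap for example if costs are skewed. Report the difference from zero as supportive.
2. **Section 2.2.** Remove the noninferiority sentence, or tie it to a named endpoint with a justified margin.
3. **Thoracic-related complications.** State the hypothesis for this coprimary endpoint separately, and note that the trial is not powered for it, as section 2.6 already concedes.

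**Cost.** The expense criterion becomes stricter than a test against zero. No extra patients are needed if the inferred one-sided 0.05 is what the sponsor intended. At one-sided 0.025, 179 per group before dropout would be needed for 80% power. Section 2.13 bars changes after publication, so this needs a formal protocol correction and not just an editorial change.

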### Eligibility criteria

2.3.

#### Inclusion criteria

2.3.1.

The indications for surgical treatment included at least two of the following: (1) Haller Index (HI) greater than 3.20 or deformity had progressed by visual assessment of parents; (2) cardiac or pulmonary compression by visual assessment on CT or reduced cardiac diastolic function parameters such as E peak/A peak ratio and ventricular end diastolic volume index ratio on echocardiogram; (3) abnormal lung function by resting pulmonary function test; (4) mitral valve prolapse or arrhythmia; (5) symptoms such as repeated episodes of respiratory infections were present; (6) patients had a severe psychosocial disorder; and (7) patients or their parents had a strong desire for deformity correction.

#### Exclusion criteria

2.3.2.

Children who had not previously pass the developmental screening test such as Denver Developmental Screening Test (DDST) were not included. Patients with severe combined malformations, such as Marfan syndrome, severe cardiac malformations and Hirschsprung's disorder, were excluded. Patients who underwent secondary surgery were also excluded.

### Interventions

2.4.

After randomization into two groups, the enrolled patients will undergo routine preoperative preparation, including blood biochemical tests, and antibiotics will be administered once 30 min before surgery. All patients will undergo general anesthesia under tracheal intubation and receive T4 and T5 paravertebral nerve block. The SINTNP group will undergo left-side single-incision nonthoracoscopic-assisted Nuss surgery in accordance with our previous report (10). The TNP group will undergo thoracoscopic-assisted Nuss surgery with bilateral incisions, with the endoscopic observation hole on the right side. We need to emphasize that any child who requires the use of two bars during surgery will be withdrawn from the study cohort. After postoperative resuscitation, the patient will return to the ward and use a pain pump within 48 h after surgery.

One day after the surgery, chest radiograph bedside ward examination will be conducted. Starting from the second day after the surgery, a VAS pain score will be collected every morning. Those with a score of three or less will undergo the 100-meter walking experiment. Those who can successfully complete the 100-meter walking experiment independently and do not report any special discomfort will undergo chest radiograph examination. Those who had no obvious pneumothorax, pleural effusion, or steel plate displacement were discharged the next morning. If the child has a clear tendency toward plate allergy, such as extensive redness and swelling of the anterior chest wall skin or poor wound healing, such as incision suppuration, the patient will withdraw from the study. Their data will not be included in the analysis of pre-protocol set but will be truthfully reported and analyzed in the final research report of full analysis set.

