#### Participant timeline

2.5.3.

The time schedule of enrollment, interventions, and assessments are described in detail in a schematic diagram (Table 1).

**Table 1 T1:** Schedule of Enrolment, allocation, intervention and close-out.

Specific procedure	Enrolment	Allocation		Intervention					Close-out
Time point	D0	D0	D1	D2	D3	D4	Every day	DN	
Eligibility screen	●								
Informed consent	●								
Block randomization		●							
Preoperative examination			●						
Undergo surgery				●					
Analgesic pump				●	●				
Chest radiograph					●			●	
VAS score						●	●	●	
Walking experiment								●	
Data management									●

● The green dot indicates that this project will take place at this time point.

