## Discussion

4.

Heart injury is the most dangerous complication of pectus excavatum, so all surgeons will do their best to avoid it (12). A practical and feasible approach is to observe through thoracoscopy (13). Through thoracoscopy, the surgeon can clearly observe the process of tunnel establishment and bar passing through the sternum. Aberrant vessels detected in the mediastinal pleura could be evaded under direct visualization during mediastinal dissection with thoracoscopy (14). Additionally, it is traditionally believed that the bar needs to be fixed bilaterally to avoid displacement, so thoracoscopy usually does not add additional incisions. Thoracoscopic assistance is necessary in adults, especially in patients with recurrence, history of previous thoracic procedure or double-bar insertion (7, 15).

However, for children who undergo their first surgery and only need to use one bar in preoperative evaluation, thoracoscopic assistance may be redundant. Children's sternum is relatively soft and malleable, and separation behind the sternum is usually safe. Especially considering the recent use of single-incision Nuss surgery, thoracoscopic assistance is difficult and may not be necessary (10). We are worried that the thoracoscope entering the pleural cavity will cause additional pulmonary complications. Excessive pain and prolonged hospital stay time may reduce the quality of life of the patient and parents after surgery, while also increasing the workload and burden of clinical doctors. We hope to reduce the surgical costs and postoperative hospital stay of the patient. In a relatively underdeveloped region such as western China, a considerable proportion of patients still struggle to bear the cost of surgery (16). Therefore, we must strive to reduce their burden.

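### Children found during surgery to need two bars leave the study after randomisation, and nothing clearly keeps them in any analysis set

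*Protocol article*

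**What the plan says.** Section 2.4 (Interventions) of the protocol article contains two removal rules, in separate paragraphs.

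- **Two bars.** "any child who requires the use of two bars during surgery will be withdrawn from the study cohort". No sentence about analysis sets follows.
- **Plate allergy or poor wound healing.** For a child with a clear tendency to plate allergy, or with "poor wound healing, such as incision suppuration, the patient will withdraw from the study". Two statements about the data come next: "Their data will not be included in the analysis of pre-protocol set", but they "will be truthfully reported and analyzed in the final research report of full analysis set".

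On timing, section 2.4 begins "After randomization into two groups, the enrolled patients will undergo routine preoperative preparation", and Table 1 puts randomisation on D0 and surgery on D2. Section 2.9 says that the group label is open to doctors. Section 2.11 plans a per-protocol analysis of participants who finish the study and says "intention to treat analysis (ITT) will be used in full analysis set". It does not say which of the two is primary.

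The Discussion describes the target children as those who "only need to use one bar in preoperative evaluation". Neither the inclusion criteria (2.3.1) nor the exclusion criteria (2.3.2) contain that condition.

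**The concern.** Randomisation makes the arms comparable at allocation. A rule that later removes children because of something seen or decided in the operating room undoes this if removal depends on the arm. Here it can. The surgeon knows the allocation, one arm has thoracoscopic vision and two incisions, and the other has a single incision and no thoracoscope. The judgement that one bar is not enough may therefore be reached at different rates, or in different kinds of children, in the two arms.

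If the removed children also differ in expense, complications or stay, the remaining groups differ for reasons other than the assigned operation. An intention-to-treat analysis normally repairs this, but only if the removed children are in it. For the two-bar cases the text does not put them there.

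For plate reaction and suppuration the problem is smaller. The full analysis set keeps them. The per-protocol set loses their expense and any effusion, pneumothorax or pneumonia they had. That matters in so far as the per-protocol result may carry the conclusion, which section 2.11 leaves open.

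**Working it through.** **Step 1. Which child is in which set, as written**

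| Reason for removal | When | Per-protocol set | Full analysis set |
|---|---|---|---|
| Two bars needed | During surgery | Out (withdrawn) | Not stated |
| Plate reaction | After surgery | Out (stated) | In (stated) |
| Wound suppuration | After surgery | Out (stated) | In (stated) |

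All three follow randomisation. Only the first has no stated place in the full analysis set.

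**Step 2. Is suppuration a primary event?** The abstract includes incision infection among thoracic-related complications. Section 2.5.1 and Table 2 list only pleural effusion, pneumothorax and pneumonia. Under the abstract, the per-protocol set drops a co-primary event by rule. Under section 2.5.1 it drops only whatever other events that child had, and the expense.

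**Step 3. Reproduce the sample size (section 2.6)**

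Inputs: means 30,250 and 28,157 RMB, SD 2,000, margin 1,500.

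- Assumed saving: 30,250 − 28,157 = 2,093 RMB.
- Distance beyond the margin: 2,093 − 1,500 = 593 RMB.
- n per group = 2 × (1.645 + 0.842)² × 2,000² / 593² = 140.7, so 141. This matches the plan with one-sided alpha 0.05 and 80% power. Neither is stated; they are inferred because they return 141.
- 160 per group allows for 1 − 141/160 = 11.9% loss, inside the stated 10% to 15%.

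**Step 4. How far could removal move the expense result?**

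The documents give no removal rate by reason or arm, and no expense for removed children. Both inputs below are assumptions. If a share w of an arm is removed and those children cost E more than the rest, the mean of the retained children is lower than the mean of all by w × E. The shift in the difference between arms is (w in SINTNP − w in TNP) × E.

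| Difference in removal | E = 3,000 RMB | E = 5,000 RMB |
|---|---|---|
| 0 points | 0 | 0 |
| 2 points | 60 (10% of 593) | 100 (17%) |
| 5 points | 150 (25%) | 250 (42%) |

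The shift favours SINTNP if more children are removed there, and TNP if more are removed there.

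**Step 5. Effect on the error rate**

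With 141 per group, the standard error is 2,000 × √(2/141) = 238 RMB. If the true saving is exactly 1,500, a shift b gives a one-sided error of 1 − Φ(1.645 − b/238):

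- b = 0: 5%
- b = +60: about 8%
- b = +250: about 28%
- b = −250: about 0.4%; the bias then works against SINTNP and costs power instead.

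**The case against.** The strongest reply is that the plan already has an intention-to-treat analysis in a full analysis set, that excluding protocol deviators from a per-protocol set is ordinary, and that set definitions are often left to a statistical analysis plan, which is not shown. This stands for plate reaction and suppuration. A reader might infer that the plan deletes these children's complications and expenses from the trial; section 2.4 says the opposite for the full analysis set. The reply does not answer the two-bar rule. The article itself withdraws those children from the cohort and attaches the retention sentence to a different rule.

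Second, no figure shows that two-bar cases differ by arm or cost more. That is right. A reader might infer that the costliest stays are removed, or that the rule favours SINTNP. The documents support neither: the range includes zero and both signs.

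Third, a reader might infer from Table 1, which places "Preoperative examination" on D1, after randomisation on D0, that randomising later would solve the problem. It would not. Nothing says that the D1 examination settles the number of bars, section 2.4 describes that step as routine preparation, and the rule is triggered during surgery.

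**Conclusion.** The point holds for the two-bar rule. It removes children after randomisation on an unmasked, arm-dependent judgement, and the text does not keep them in the full analysis set. If it is followed as written, the comparison of expense, complications and stay is no longer a fully randomised one.

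For plate reaction and suppuration it holds only for the per-protocol set. Whether the infection itself is a lost primary event depends on which of the article's two definitions applies.

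The size of the bias cannot be found from the documents. Under the assumptions of a 0 to 5 point difference in removal and 3,000 to 5,000 RMB excess cost, it is 0 to 250 RMB in either direction, at most 42% of the 593 RMB on which the sample size rests. Equal removal at equal excess cost gives no shift.

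**What to change.** 1. In sections 2.4 and 2.11, state that every randomised and operated child, including two-bar, plate-reaction and suppuration cases, stays in the full analysis set in the assigned arm, with outcomes collected to discharge.
2. In section 2.11, name that set as the primary analysis for both co-primary outcomes.
3. Treat the per-protocol analysis as supportive, and do not remove children from it because of a postoperative complication.
4. Reconcile the eligibility criteria in 2.3 with the Discussion's population of children judged before surgery to need one bar. This makes the population consistent; it does not replace item 1, because the need for a second bar can still emerge during surgery.

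**Cost.** The change is a few sentences. Section 2.13 prohibits changes after publication, so it needs a formal, documented amendment.

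No larger sample follows from the plan's own inputs. With SD 2,000 and one-sided alpha 0.05, power is Φ(593 / (2,000 × √(2/n)) − 1.645): 84.3% with all 160 per group, against 80.8% with 144 (10% loss) and 78.8% with 136 (15% loss).

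Retained two-bar stays add some variance. If the SD of 2,000 describes one-bar stays only and a share w costs E more in both arms, the SD becomes √(2,000² + w(1 − w)E²). For w = 2% and E = 3,000 it is 2,044, with power about 83% at 160 per group. For w = 5% and E = 5,000 it is 2,278, with power about 75%. The first is minor. The second is an upper case under assumed inputs, and the sponsor can check it against the retrospective expense data behind section 2.6.
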